#### Secondary Outcomes

##### Perceived Diabetes Self-Management Scale

The original questionnaire was developed by Wallston et al [43]. It consists of 8 items scored on a 5-point Likert scale ranging from 1 (strongly disagree) to 5 (strongly agree), of which items 1, 2, 6, and 7 are reverse scored. The total score ranges from 8 to 40, with higher scores indicating higher confidence in diabetes self-management. Lin et al [44] translated the scale into Chinese to assess 168 patients with T1D and type 2 diabetes (T2D). The translated questionnaire has content validity, Cronbach α, and test-retest reliability values of 0.75, 0.93, and 0.97, respectively.

##### Self-Care Behavior Assessment Scale

This scale was originally developed in Chinese by Wang [45] to measure self-care behaviors of adolescents with T1D. It comprises 7 dimensions: pharmacological treatment–insulin injections; healthy diet–diet control; blood glucose monitoring–self-monitoring; physical activity and exercise–regular exercise; problem-solving–risk reduction; healthy coping–psychological and social adaptation; and stress adaptation. A total of 39 items are scored on a 5-point Likert scale ranging from 1 (not achieved at all) to 5 (completely achieved), of which items 26 to 35 are reverse scored. The total score ranges from 39 to 195, with higher scores indicating better self-care behaviors. Cronbach α and the content validity value are 0.87 and 0.92, respectively.

##### Diabetes Distress Scale

The original scale was developed by Polonsky et al [46]. The Chinese version consists of 17 items across 4 subscales: emotional burden, physician-related distress, regimen-related distress, and diabetes-related interpersonal distress. Items are scored on a 4-point Likert scale ranging from 1 (no distress) to 4 (severely distressed), with higher scores indicating more severe emotional distress. Cronbach α and test-retest reliability values of the Diabetes Distress Scale are 0.89 and 0.81, respectively [47].

##### Diabetes Quality of Life

The original scale was developed for use in the Diabetes Control and Complications Trial and translated into Chinese by Cheng et al [48]. The Chinese version consists of 42 items with the following subscales: satisfaction, impact, and diabetes-related worry. Each item is scored on a 5-point Likert scale, with 1 and 5 representing “very dissatisfied” and “very satisfied” in the satisfaction subscale, “never” and “always” in the impact subscale, and “never worried” and “always worried” in the diabetes-related worry subscale, respectively. Higher scores are indicative of a higher QoL. The Cronbach α and test-retest reliability values of the scale and subscales are within the ranges of 0.76-0.92 and 0.94-0.99, respectively.

##### Diabetes Knowledge Questionnaire

The original questionnaire was developed by Garcia et al [49]. The Chinese version comprises 24 items that are answered “Yes,” “No,” or “I don’t know”; 1 point is awarded for each correct answer. The total score ranges from 0 to 24 points, with higher scores indicating more excellent knowledge of diabetes. In a study that adopted the 24-item Diabetes Knowledge Questionnaire (DKQ) for assessing 108 patients with T2D, the results indicated reliability and Cronbach α values of 0.78 and 0.89, respectively [50]. Currently, the DKQ is used chiefly for patients with T2D. However, when we sequentially inspected all items of the DKQ to determine its applicability to patients with T1D, it was found that the correct answer for Item 6, “If I am diabetic, my children have a higher chance of being diabetic,” needs to be changed to “No,” and for Item 13, “Medication is more important than diet and exercise to control my diabetes,” needs to be changed to “Yes.” In contrast, the remaining items and answers remain applicable to patients with T1D and are considered essential knowledge among such patients. Therefore, the DKQ will be used in this study following the above-mentioned modifications.

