#### Knowledge Gaps

Currently, the available apps for diabetes management can be broadly classified into 5 categories: nutrition, physical activity, blood glucose monitoring, insulin titration, and insulin injection. Most apps merely possess a single function, although there is an increasing trend toward integration [37]. Additionally, the majority of Chinese-language apps provide general diabetes knowledge, which may not be applicable to adolescents or young adults, and do not cater to the specific needs of patients with T1D in the transition phase [5]. Furthermore, the effectiveness of such apps should be validated by long-term empirical evidence [24,38], and few studies have mentioned the adoption of strategies to enhance treatment fidelity [31,35]. Health apps developed for intervention should incorporate evidence-based content while fulfilling the needs and protecting the privacy of the target age groups to enhance effective disease self-management [39]. To address the specific needs of patients in the transition phase, we developed the Healthcare CEO app using a user-centered approach. This app targets challenges such as poor glycemic control; pressures related to self-care; effective disease self-management; and interpersonal issues, including the establishment of romantic relationships, concerns about the health and heredity of future generations, workplace adaptation, parent-child conflicts, and enhancing QoL. This study aims to present a comprehensive protocol for evaluating the efficacy of the Healthcare CEO app. This will involve a series of detailed analyses, including (1) comparing disease control outcomes, confidence in self-management, self-care behaviors, emotional distress, and QoL between the experimental and control groups, and (2) a comparison of differences in preintervention and postintervention disease control outcomes, confidence in self-management, self-care behaviors, emotional distress, and QoL in the experimental group.

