**Figure 2 figure2:**
[figure not shown]
Interfaces of the Healthcare CEO app. CEO: chief executive officer.

**Table 1 table1:** Content of Healthcare CEO app.

Interface	Description of content	Purposes and expected outcomes
CEO’s Profile	Personal and disease data, including the following: name, nickname, date of birth, occupation, duration of disease, hospital, and attending physician. The patient can select the data to be openly displayed.	Establish basic data Review and confirm basic disease information through data entry
Health Tracking	Upload or enter data on blood glucose level, blood pressure, body weight, and insulin dosage. HbA_1c_^a^ targets can be set, and changes in HbA_1c_ can be analyzed and displayed as trends.	The status of HbA_1c_ control can be checked to enhance self-care motivation and confidence in disease self-management
CEO Knowledge Base	Basic and advanced knowledge of interest to patients with T1D^b^ in the transition phase is provided in the e-book format. Examples of basic knowledge include the following: impact of secondary sex characteristic development on blood glucose; blood glucose control targets in T1D; and tips for dieting, exercise, and travel during puberty. Examples of advanced knowledge are as follows: matters related to sex, genetics, gestation, and employment among patients with T1D. Both a pretest and posttest must be completed to determine the learning effectiveness of each article before the next article can be accessed.	Patients can enhance T1D-related knowledge on a need basis Patients can boost their confidence in disease management by accumulating disease-related knowledge. This will enhance self-care behaviors, disease control outcomes, and disease-related QoLc
Barrier-free Communication	Guidance for techniques in parent-child, peer, and workplace interactions is provided through video and e-book links. Questions and scenarios are designed to prompt patients to reflect on their communication methods and think about/enact their strategies for effective interaction.	Improve communication skills, enhance ability to deal with interpersonal difficulties, and reduce emotional distress

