### Validity and Reliability

The study design and participant enrollment process were formulated in accordance with the recommendations of the CONSORT (Consolidated Standards of Reporting Trials) statement. We also formulated strategies based on the National Institution of Health Behavior Change Consortium guidelines to monitor the faithfulness and fidelity of the intervention process. The research tools used in this study also exhibit good validity and reliability. In the measurement of the primary outcome variables, this study differs from previous works on diabetes management apps in that “% with HbA_1c_ <7.0%” data will be calculated for the first time for analysis. This allows for greater objectivity and rigor in evaluating the effectiveness of the Healthcare CEO app.

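### Item 6 of the Diabetes Knowledge Questionnaire is re-keyed to credit only *No* on raised risk in offspring, without a stated basis, while genetics is taught in one arm only

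*Protocol article*

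**What the plan says.** All of the scoring rules are in the protocol article, Secondary Outcomes, Diabetes Knowledge Questionnaire. The Chinese version has 24 items answered *Yes*, *No* or *I don't know*, and "1 point is awarded for each correct answer". The direction is fixed: "The total score ranges from 0 to 24 points, with higher scores indicating more excellent knowledge of diabetes". Because the instrument is mainly used in type 2 diabetes, the team went through its items and altered two answers. For item 6 the text reads "If I am diabetic, my children have a higher chance of being diabetic,” needs to be changed to “No". For item 13, on medication versus diet and exercise, the correct answer becomes *Yes*. The changes are operative: "Therefore, the DKQ will be used in this study following the above-mentioned modifications".

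Three other places bear on item 6:
- Table 1 describes the CEO Knowledge Base: "Examples of advanced knowledge are as follows: matters related to sex, genetics, gestation, and employment among patients with T1D".
- Knowledge Gaps lists among the app's targets "concerns about the health and heredity of future generations".
- Control App Intervention limits controls to the profile and health-tracking interfaces. They may have the full app only after the last data collection.

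Validity and Reliability then says of the instruments as a whole: "The research tools used in this study also exhibit good validity and reliability".

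**The concern.** Item 6 is a comparative statement. *No* is the correct answer only if the children of a person with diabetes are at no greater risk than others. A low absolute risk, or inheritance that is far from certain, would not make *No* correct. The protocol gives no source, expert rating or reasoning for the reversal, so an answer that appears to be false earns the point and the answer that appears to be true earns none.

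A mis-keyed item that affects both arms equally would mostly add noise. Here the subject of the item is taught in one arm and withheld from the other until the trial ends. The error can therefore enter the between-arm difference in knowledge, and also the before-after change within the experimental arm, which the Statistical Analysis section plans to report.

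**Working it through.** **What the documents fix**

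| Input | Value | Place |
|---|---|---|
| Key for item 6 | *No* | Diabetes Knowledge Questionnaire |
| Key implied before the change | *Yes* | same section (it is changed to *No*) |
| Points per item, number of items | 1, 24 | same section |
| Genetics content, experimental arm | yes, as an advanced topic | Table 1 |
| Genetics content, control arm | none during the trial | Control App Intervention |
| What the app says about offspring risk | not stated | – |
| Offspring risk | not stated; only a population prevalence of 0.05% at age 19 or younger | Introduction, Overview |

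The plan's own range reproduces: 24 items × 1 point = 24. Item 6 is 1/24 = 4.2% of that range. The sample size does not depend on this item.

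**Effect on one participant.** Take a participant who comes to believe that the risk is raised.
- From *No* to *Yes*: the score changes by −1 under the key *No* and by +1 under the key *Yes*, a swing of 2 points between keys.
- From *I don't know* to *Yes*: the score changes by 0 under the key *No* and by +1 under the key *Yes*. Nothing is lost, but the gain is not credited.

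**Effect on the between-arm mean.** The contribution of item 6 is

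P(keyed answer | experimental) − P(keyed answer | control).

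The documents give no response rates, so the shifts below are assumptions that show the range. They describe the experimental arm relative to control.

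| Assumed shift | Key *No* | Key *Yes* | Swing |
|---|---|---|---|
| none | 0 | 0 | 0 |
| 10% from *No* to *Yes* | −0.1 | +0.1 | 0.2 |
| 30% from *No* to *Yes* | −0.3 | +0.3 | 0.6 |
| 20% from *I don't know* to *Yes* | 0.0 | +0.2 | 0.2 |
| 30% from *Yes* to *No* (app teaches the new key) | +0.3 | −0.3 | 0.6 |
| everyone from *No* to *Yes* (extreme) | −1 | +1 | 2 |

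For example, with 40% *No* in control and 10% in the experimental arm, the key *No* gives 0.1 − 0.4 = −0.3. With 40% *Yes* in control and 70% in the experimental arm, the key *Yes* gives 0.7 − 0.4 = +0.3.

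The sign depends on the content of the genetics article, and the size depends on how many participants read it and change their answer. Neither is in the documents.

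**The case against.** The strongest reply is that the documents never state the risk to offspring, so they cannot by themselves show that *No* is false. Patients' worries about heredity are not evidence of raised risk, and the population prevalence is only one half of a comparison. This stands as a limit: the judgement that *Yes* is correct rests on general medical knowledge. It does not rescue the key, because the item is comparative and the protocol offers nothing in support of *No*.

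A reader might also infer several stronger things that the documents do not support:
- *That experimental participants will lose points for learning true facts.* Table 1 only names genetics as an example topic, and the protocol says articles are used as needed. The app could equally teach the new key. A point is lost only by someone who would otherwise have answered *No*.
- *That the bias is a known fraction of the planned effect.* No standard deviation for the DKQ is given, and the effect size in the Sample Size section is not tied to this scale.
- *That the total no longer measures knowledge.* One item of 24 is in doubt, and nothing here speaks against the 22 items that were not altered.
- *That the item 13 key is also wrong.* No case for that has been made. It matters here only because it too was changed by inspection alone.
- *That the reliability figures are presented misleadingly.* The DKQ section openly says that they come from patients with type 2 diabetes and that two answers were changed. What remains is that they do not cover the re-keyed version, so the general statement under Validity and Reliability reaches too far for this score.

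**Conclusion.** The concern holds in a limited form. The protocol fixes a scoring rule for item 6 that has no stated basis and appears to be wrong. Genetics teaching reaches only the experimental arm during the trial, so the rule can distort the knowledge comparison in either direction. The limit is 1 of 24 points per participant (4.2% of the range), or 2 points of swing between the two keys. Realistic shifts would move the arm difference by a fraction of a point.

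Two things are assumed: that familial risk in type 1 diabetes is raised, which the documents neither state nor contradict, and that the app's genetics content changes some answers. One secondary outcome is affected. The primary outcomes and the sample size are not. The point should be corrected before analysis, but it does not threaten the trial's main conclusions.

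**What to change.** 1. Do not credit *No* on item 6 in the main knowledge score. There are three acceptable ways: score without item 6 (range 0-23), score without both re-keyed items (0-22), or restore *Yes* for item 6 after checking it against the app's genetics article and that article's own pretest and posttest.
2. Choose one of these before the arms are compared, and apply it to the stored item answers of all participants, including those already enrolled.
3. Report the total under the other key as a sensitivity analysis, and give the reason or source for each altered answer.
4. State that the quoted reliability values (0.78 and 0.89) come from patients with type 2 diabetes and do not cover the re-keyed version.

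The cost is a change to the scoring key and one rescoring run. No new data are needed, provided that the online questionnaire kept item-level answers, which its mandatory fields make likely. A 22- or 23-item total is slightly less comparable with published 24-item totals.

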#### App Use Data

During the data collection period, the administrators will also download app-use data at the backend. Such data include log-ins to the Healthcare CEO app, the number of e-books read in the CEO Knowledge Base, the number of online consultations with the CEO’s Secretary, and the content of the chats in the CEO Chat Rooms.

### Data Collection

Three research assistants with a background in health care, who have a basic understanding of T1D, have undergone training, and are not involved in the provision of health care, will be responsible for the data collection. Attending physicians of patients with T1D will provide referrals of patients who meet the inclusion criteria. One research assistant in charge of data collection will then approach the patients to explain the purposes of the study and the research process. Patients who agree to participate will subsequently fill out the informed consent sheet and undergo the preintervention test (T0) in an undisturbed environment. The second research assistant will obtain the randomization results from the statistician by phone and assist participants in downloading the Healthcare CEO app onto their smartphones based on their group assignment. The third research assistant will check and remind the second research assistant of the intervention steps to ensure the accuracy and completeness of the intervention. Considering that HbA_1c_, the critical indicator of blood glucose control, is measured once every 3 months, the time points for the postintervention data collection for both groups are set at 3 months (T1), 6 months (T2), and 9 months (T3) after the intervention.

### Treatment Fidelity

#### Overview

To monitor the faithfulness and fidelity of the intervention process and enhance intervention effectiveness evaluation, we formulated strategies for the inspection of treatment fidelity in the 5 areas proposed by Bellg et al [51] at the National Institution of Health Behavior Change Consortium.

#### Treatment Design

A standard treatment manual was formulated to explain the purpose of the study, the processes, and the details. Standardized interaction content of the interventions was established.

#### Training Provider

Research assistants received 16 hours of standardized training in accordance with the roles they will serve in the study. The standard training sessions attended by all research assistants included treatment of patients with T1D in the transition phase, research ethics, and 2 observational visits to the outpatient clinic for familiarization with the study settings. Individual training sessions included data collection techniques or the development, methods of use, and troubleshooting of the Healthcare CEO app. In addition, during the data collection process for the first 10 participants, the research assistants will be accompanied by senior researchers to confirm their techniques and abilities in participant inclusion and ensure faithfulness in the implementation of the intervention measures, and strategies for improvement will be provided after observation.

#### Delivery of Treatment

An intervention step checklist has been formulated and will be provided to research assistants for the sequential inspection and confirmation of the level of completion and completeness of the intervention measures. Another assistant will inspect the fidelity and faithfulness of the intervention process using an intervention process checklist and perform voice recordings of the entire treatment process for researchers to conduct random analyses, evaluations, and feedback.

#### Receipt of Treatment

Participants will be asked to perform operations in the app and discuss and clarify any doubts that they may have. An intervention content checklist will be provided to the participants after the completion of the intervention to confirm that they have received the complete intervention and determine their level of understanding and app use abilities.

#### Enactment of Treatment Skill

To ensure that participants are capable of using the app in everyday life, the following will be carried out: weekly monitoring of the frequency of app content usage and the level to which app usage has been correctly completed, documenting usage issues and suggestions highlighted by participants during routine telephone follow-up, and downloading and analyzing app use data during each round of data collection.

### Data Analysis

#### Statistical Analysis

The intention-to-treat principle will be used for the data analysis; that is, all participants will be included in their initially assigned groups for analysis, regardless of whether they withdraw from the study for any reason or are lost to follow-up. Data will be analyzed using IBM SPSS 26.0 for Windows, with differences considered statistically significant at *P*<.05. Demographic and disease status data, including age, gender, BMI, age at diagnosis, disease duration, and HbA_1c_, along with metrics on the app usage to evaluate treatment fidelity, such as the log-ins to the app, frequency of use for each interface, number of e-books read in the CEO Knowledge Base, and number of online consultations in CEO’s Secretary, will be presented through descriptive statistics. This will include frequency distributions, percentages, means, SDs, and maximum and minimum scores. Homogeneity in the essential attributes of the 2 groups will be compared and analyzed using inferential statistics, such as the chi-square test and ANOVA. Owing to the longitudinal nature of this study, repeated data measurements will be taken. Dependencies may exist among the data at different time points, and data loss may also occur. Using generalized estimating equation models, repeated measurements can be simultaneously included in the regression analysis. Through the variance correction process, consistent estimates of the regression parameters and their variance can be provided to correct for dependencies, and participants with missing values can still be included in the analysis [52]. Therefore, a generalized estimating equation will be used for data analysis to compare the differences between the experimental and control groups at both preintervention and postintervention time points, as well as the differences in the scores of the experimental group before and after intervention.

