#### Sample Size

The required sample size was estimated using the G*Power program (Heinrich-Heine-Universität Düsseldorf) for repeated measures with 2 groups, 9 measured variables, power of 0.80, α set at .05, an estimated Cohen effect size of 0.25, and a correlation coefficient of 0.5. The sample size for each group was calculated as 36. By allowing for a potential 25% dropout rate, as suggested by Goyal et al [31], a final sample size of 96 participants (48 participants in each group) was established.

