### Randomization and Blinding

Randomization of the participants will be performed by a statistician, using the central randomization method in SPSS (IBM Corp). During participant enrollment, participants will be randomly assigned to the experimental or control groups in accordance with the instructions provided on the phone by the statistician; the participants and data collectors will be blinded to allocation. Blinding strategies include the following. First, the statistician will not be allowed to disclose the randomization results to others. Second, once a physician referral is received, the participant will be promptly taken to a private room. The data collection assistant will complete their duties and leave the room, and then 2 research assistants will come in and take over to administer the intervention phase. Third, participants of both the experimental and control groups will download the app, but the app content will differ. Fourth, to avoid differential demand characteristics, research assistants will emphasize to all participants that app usage is potentially beneficial for disease management.

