#### Demographic Questionnaire

This self-designed questionnaire has been developed based on the conceptual framework of this study. It includes questions on age, sex, BMI, educational level, occupation, number of hospital stays, complications, age at diagnosis, duration of diabetes, frequency of blood glucose self-monitoring, department responsible for follow-up, number of physician changes, and number of department changes.

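### Chi-square and ANOVA tests of baseline homogeneity cannot show that two randomised arms are comparable and do nothing to protect the treatment contrast; pre-chosen covariates would

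*Protocol article*

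**What the plan says.** In the Statistical Analysis section, the baseline check is one sentence: "Homogeneity in the essential attributes of the 2 groups will be compared and analyzed using inferential statistics, such as the chi-square test and ANOVA". The same section sets a single threshold for all analyses, "differences considered statistically significant at *P*<.05". It names the baseline attributes to be described as "Demographic and disease status data, including age, gender, BMI, age at diagnosis, disease duration, and HbA_1c", which makes six. The Demographic Questionnaire section gives a longer list of 13, beginning: "It includes questions on age, sex, BMI, educational level, occupation, number of hospital stays, complications, age at diagnosis, duration of diabetes".

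Allocation is by chance. The Randomization and Blinding section states: "Randomization of the participants will be performed by a statistician, using the central randomization method in SPSS (IBM Corp". The Sample Size section gives the numbers to be compared: "a final sample size of 96 participants (48 participants in each group) was established", inflated from 36 per group for 25% dropout.

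The treatment comparison itself is a generalised estimating equation (GEE) that takes in pre- and post-intervention time points. The article does not say what follows from a significant or a non-significant baseline test.

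**The concern.** The stated purpose of the tests is to assess homogeneity of the arms. A significance test cannot do this in a randomised trial, for two reasons.

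First, the hypothesis tested is that both arms come from one population. Sound randomisation makes that true, so the test can only be right by not rejecting. A rejection signals chance, unless allocation was subverted.

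Second, a large P value does not show that the arms are alike. Whether an imbalance matters depends on its size and on how strongly the attribute predicts the outcome, and a P value measures neither. The article gives no margin or standardised difference by which the arms would count as comparable, so P<.05 is the only yardstick in the text.

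At stake is mainly a missed opportunity. The planned check leaves the app-versus-control estimate exactly as it was, whereas adjustment for prognostic variables already collected would sharpen it and guard against chance imbalance. There is also a risk that readers or authors take P≥.05 as proof of equivalence, or take a stray significant result as a failure of randomisation.

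**Working it through.** **Inputs.** 48 per arm enrolled and 36 per arm after dropout (Sample Size); α = .05 (Statistical Analysis), taken as two-sided, because a two-group ANOVA is equivalent to a two-sided t test; 6 and 13 attributes (Statistical Analysis; Demographic Questionnaire).

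**The plan's own sample size.** The section specifies "repeated measures with 2 groups, 9 measured variables, power of 0.80, α set at .05, an estimated Cohen effect size of 0.25", with correlation 0.5. For the between-groups effect in repeated-measures ANOVA, λ = N·f²·m/(1+(m−1)ρ) = 72 × 0.0625 × 9/(1 + 8 × 0.5) = 8.1, with 1 and 70 degrees of freedom. Power is 80.1%, so 36 per group reproduces. Dropout: 36/(1 − 0.25) = 48 per group, 96 in total, which also reproduces. The figures of 48 and 36 are therefore sound inputs for this check.

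**What a non-significant result allows.** The largest observed difference, in SD units, that stays non-significant is t(.975, 2n−2) × √(2/n).

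- n = 48: 1.986 × 0.2041 = 0.405 SD
- n = 36: 1.994 × 0.2357 = 0.470 SD

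The Results section reports 13 participants per group at present. At n = 13 the limit is 2.064 × 0.3922 = 0.81 SD, so at that size a homogeneity P value carries almost no information.

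**What a significant result means.** With sound randomisation each test rejects about 5% of the time. The chance of at least one rejection among k independent tests is 1 − 0.95^k.

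- k = 6: 1 − 0.95⁶ = 0.265
- k = 13: 1 − 0.95¹³ = 0.487

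Independence is an assumption and is not strictly met: age is age at diagnosis plus disease duration. Whatever the dependence, the chance cannot exceed 6 × 5% = 30% for six tests or 13 × 5% = 65% for thirteen.

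**Effect on the treatment contrast.** Let the baseline attribute correlate ρ with the outcome, let there be no app effect, and let the observed imbalance be d. An unadjusted single-visit contrast is then distributed about ρd with variance (1−ρ²)·2/n, and is rejected beyond 1.96·√(2/n). Values of ρ are assumed.

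- Given d = 0.4 at n = 48: 12.9% rejections at ρ = 0.5 (7.9% at ρ = 0.3, 20.5% at ρ = 0.7).
- Averaged over all imbalances that pass the test at n = 48: 4.3% at ρ = 0.5.
- Averaged over all randomisations: 5%.

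So a particular unlucky allocation can distort an unadjusted contrast while passing the test, but passing the test does not raise the error rate on average.

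**The case against.** The strongest reply is that the tests are harmless. The article does not equate a non-significant result with equivalence, does not call a significant one failed randomisation, and does not select covariates from them. Comparability rests on central randomisation, and descriptive statistics are planned for the same attributes. Deleting the tests changes no estimate or interval. All of this stands, and it is why the point is minor.

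Three stronger readings are tempting and should not be made.

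- A reader might compute that a 0.5-SD imbalance is missed 32% of the time at 48 per arm. That is the t test's failure rate for a true population difference, and randomisation leaves none to miss. An observed 0.5-SD difference gives t = 0.5/0.2041 = 2.45, P = .016, and is always flagged. The relevant limit is 0.405 SD.
- A reader might infer that the plan inflates the false-positive rate to about 13%. That figure is conditional on an imbalance of 0.4 SD, just below the limit, and on an unadjusted single-visit contrast. The average is not above 5%. The planned GEE also includes the pre-intervention time point, so a comparison of change would at least partly account for baseline HbA1c, though not for disease duration.
- A reader might infer data-driven adjustment. The text states no such rule.

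It can also be said that covariate choice belongs in the full analysis plan, which is not shown. Its absence here is indeed no finding. The finding is the method that is stated, a significance test for a purpose it cannot serve; covariates enter only as what would serve that purpose.

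**Conclusion.** The point holds as a minor one, and acting on it is a cheap improvement. The baseline tests cannot establish homogeneity in either direction. With sound randomisation, roughly one trial in four would show at least one significant attribute over the six named (one in two over thirteen) by chance alone. Observed differences up to 0.41 SD at 48 per arm, or 0.47 SD at 36, would go unflagged. The tests give no protection to the treatment contrast; adjustment for prognostic baseline variables does. Inferred equivalence and data-driven adjustment are risks in use, not stated plans.

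These figures assume two-sided tests, correct allocation, equal arms and, for the 26% and 49%, independent attributes.

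**What to change.** In the Statistical Analysis section, replace the homogeneity sentence with text to this effect:

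*Baseline attributes will be described by arm (mean and SD, or n and %) with standardised differences. No significance tests of baseline differences will be done, and comparability will not be inferred from P values. The between-group GEE models will include age and disease duration as fixed covariates, regardless of observed imbalance.*

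Add one sentence on the baseline value of each outcome, including HbA1c, so that it is used once: either as a covariate with T1 to T3 as the outcomes, or as the T0 outcome row with the group-by-time contrast, but not both in the same model. Age at diagnosis need not be added, since it follows from age and duration.

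The cost is a change of wording and a few model terms. Age and disease duration are already in the baseline questionnaire. The downside is a few degrees of freedom and no P value column in the first table.
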